#### Gut microbiota study outcome

This ancillary study will be optional so that it does not hinder patient participation. Patients will be offered to participate in the ancillary study at baseline.

*Gut microbiota* [Time points: D0, end CT (M3), M12, and Y3]: Gut microbial diversity and taxonomic composition will be measured using full-length 16 S rRNA gene amplicon sequencing on DNA extracted from faecal samples [49]. Faecal samples will be taken using a FIT kit (OC-Auto Sampling tubes, Eiken, Japan) which includes all the necessary equipment for collecting. The first faecal sample will be taken in the hospital at the start of chemotherapy. The other samples will be taken by the patient at home. This kit will be given to the patient during the visits. Once the sample has been taken, the patient must indicate the date and time of the sample on a questionnaire and use a stamped envelope to send the sample and the questionnaire to the University of Lyon 1, responsible for storing and analysing the data. The mailing should be done as soon as possible, ideally within 24 h of the collection. The faecal sample received by post should be frozen and stored at -80 °C before NDA extraction. Total DNA will be extracted from the faecal samples using the PowerFecal DNA Isolation kit (MoBio Laboratories, Carlsbad, CA, USA). DNA extracts will be stored at -20 °C before use. The 16 S rRNA V1-V9 gene will be amplified and sequenced using Oxford nanopore technology (3rd generation sequencing) [49]. The sequence data will be processed bioinformatically using a pipeline within QIIME2 [50, 51] to calculate (1) the relative abundance (%Amplicon Sequence Variant, ASV) of bacterial taxa, (2) within-sample (alpha-) diversity using the phylogenetic tree indices of Chao1, Shannon and Faith phylogenetic tree indices, and (3) between-sample (beta-) diversity using Bray-Curtis and unweighted and weighted UniFrac distance matrices.

*Gut microbiota-derived metabolites* [Time points: D0, end CT (M3), M12, and Y3]: Metabolites involved in the gut-brain axis (e.g., SCFAs, bile acids, GABA, tryptophan metabolites including serotonin) will be measured in serum using targeted and untargeted metabolomic approaches [52, 53]. Blood samples will be taken at the investigating centres during patients’ visits (at inclusion, at the end of chemotherapy, at one year and at 3 years). Subjects will be asked to come in fasting for at least 8 h. Blood will be collected in two vacutainer SST tubes of 6 ml. The tubes containing the blood will be left at room temperature (and protected from light if possible) for one hour and then centrifuged at 30,000 rpm for 10 min at room temperature. The serum will then be aliquoted into tubes provided by the sponsor (500 µL in each tube). Serum aliquots will be stored at -80°c before use. First, SCFAs, bile acids, GABA, and tryptophan metabolites including serotonin will be measured in the blood (serum) using targeted metabolomics approaches: SCFAs by derivation of 1-(tert-butyldimethylsilyl) imidazole (MTBSTFA) and analysis by gas chromatography (GC) [52]; Bile acids, GABA and tryptophan metabolites including serotonin will be measured by liquid chromatography-tandem mass spectrometry (LC-MS/MS) in combination with the kit Biocrates MxP Quant 500 (Biocrates, Innsbruck, Austria). Other non-target microbial metabolites will be measured by ultra-high-performance liquid chromatography-quadrupole time-of-flight mass spectrometry (UHPLC-QTOF-MS).

*Medication and supplement intake* [Time points: D0, end CT (M3), M12, and Y3]: Drugs or supplements (e.g., antibiotics, metformin, proton pump inhibitors, laxatives, probiotics) [54, 55] that can interfere with the gut microbiota taken for the last one month will be collected by a questionnaire. In addition, patients taking antibiotics in the previous two weeks prior to faecal sampling will be excluded from the ancillary study.

**Table 1 Tab1:** Summary of data/biological sample collection

Evaluation	Time points													
	Inclusion (D0)	End CT (M3)	M6	M12	Y2	Y3	Y4	Y5	Y6	Y7	Y8	Y9	Y10	
***Clinical Examination***														
Pain	X	X	X	X	X	X								
Tumour Evaluation		X	X	X	X	X	X	X	X	X	X	X	X	
Cardiovascular toxicities				X	X	X	X	X	X	X	X	X	X	
Second primary tumour				X	X	X	X	X	X	X	X	X	X	
***Questionnaires***														
CRF (QLQ-FA12)	X	X	X	X	X	X	X	X	X	X	X	X	X	
HRQoL (QLQ-C30/TC26)	X	X	X	X	X	X	X	X	X	X	X	X	X	
Cognition (FACT-Cog)	X	X		X	X	X								
Anxiety/depression (HADS)	X	X	X	X	X	X								
PA/sedentary levels (ONAPS-PAQ)	X	X	X	X	X	X	X	X	X	X	X	X	X	
Pain and neuropathies (VAS)	X	X	X	X	X	X								
Nutrition (WCRF)	X	X	X	X	X	X								
Sustainable return to work				X	X	X								
Motivation (EMAPS)	X	X		X										
Satisfaction with the connected activity tracker				X										
Satisfaction with the intervention				X										
Practice locations	X													
***Physical condition/fitness***														
6-min walk test	X	X	X	X	X	X								
Sit-to-stand test	X	X	X	X	X	X								
Handgrip test	X	X	X	X	X	X								
Anthropometrics	X	X	X	X	X	X								
Number of steps per day (connected activity tracker)	Every day, non-stop (up to M12)													
Heart rate (connected activity tracker)	Non-stop (up to M12)													
Sleep quality (connected activity tracker)	Non-stop (up to M12)													
***Gut microbiota study***														
Blood sampling	X	X		X		X								
Optional faecal sampling	X	X		X		X								
***Blood biomarkers***														
Gut microbial metabolites	X	X		X		X								
Inflammation/Immunity	X	X		X		X								
Liver function	X	X		X		X								

## Statistical considerations

### Sample size

In order to evaluate our primary endpoint and to detect a minimum significant difference ≥ 10 points in the CRF scores between the 2 groups at 3 years, with a standard deviation of 20, considering 2 dimensions of CRF (physical and cognitive fatigue) assessed by the EORTC QLQ-FA12 questionnaire, with a bilateral alpha, type I error of 0.025 (Bonferroni adjusted *p*-value for two targeted dimensions, overall risk of 5%), a statistical power of 90%, 200 patients with fatigue scores available at baseline and 3 years is required. Considering 15% of lost to follow-up or unavailable data and patients without fatigue scores available, 118 patients per group will be randomized (1:1), for a total of 236 patients.

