### Study objectives

Objective 1: to investigate the impact of a one-year supervised PA program implemented concomitantly with first-line cisplatin-based chemotherapy, on CRF (primary outcome, both physical and cognitive aspects of CRF at 3 years) and other short- and long-term sequelae (secondary outcomes: another dimension of CRF– emotional fatigue, HRQoL, cognition, anxiety/depression, anthropometry, physical condition, PA/sedentary behaviour level, pain and neuropathy, sustainable return to work, sleep quality, heart rate, TGCT relapse, cardiovascular toxicities, secondary primary malignancy, immune/inflammatory/liver function biomarkers) in first-line metastatic TGCT patients (Hypothesis 1).

Objective 2: to investigate how the gut microbiota (diversity and taxonomic composition) and its metabolites involved in the gut-brain axis (e.g., SCFAs, bile acids, GABA, tryptophan metabolites including serotonin) mediate the impact of PA on primary and secondary outcomes in metastatic TGCT patients receiving chemotherapy (Hypothesis 2).

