### Statistical analysis

All statistical analyses will be performed using the R statistical software (ver. 4.3.0, R Development Core Team, 2023) and SAS (ver. 9.4, The SAS Institute, Cary, NC, USA).

Categorical variables will be described using frequency distributions and percentages. The number of missing data will be indicated, but will not be taken into account for the calculations. Quantitative data will be described using the number of observations, mean, standard deviation, median, minimum and maximum values. The date of randomization will be considered as the reference date in all time calculations unless otherwise specified. An ITT analysis will be used to avoid attrition bias. Data at inclusion will be described in the ITT population and presented by the randomization arm. Results will be considered significant when the *p*-value is less than or equal to 0.05, except for the primary endpoint (alpha set at 0.025).

For the primary endpoint, the minimal important difference (MID) will be set to 10 points for each fatigue score (physical and cognitive) (MID = 0.5*SD) [56, 57]. These dimensions of the EORTC QLQ-FA12 will be analysed at 3 years. A Student-t test will be used to compare the scores between the two arms at 3 years, adjusting for the level of HRQoL at inclusion. In case of non-normal distribution, a non-parametric Mann-Whitney test will be performed. An analysis of the missing data profile at baseline and during follow-up will be performed to determine the missing data profile. An effort will be made to have all patients complete the baseline questionnaire as well as the 3-year questionnaire, to ensure the statistical power for the primary analysis. Stratified analyses will be performed according to stratification criteria of the randomisation.

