### Decision rule

A single sufficient decision rule will be taken to interpret the results: the primary endpoint will be considered to be reached if at least one dimension among the two targeted ones (physical and cognitive fatigue) will be statistically significant in favour of the intervention arm, in absence of a statistically significant negative result on the other dimension.

For secondary endpoints, data at randomization will be compared between the 2 arms, and then the absolute and relative variations between inclusion and the different measurement times will be described and compared by arm. Longitudinal analysis of HRQoL will be performed by including all available measurement time until Y3. A mixed model for repeated measures will be performed including the randomized group, time, and intervention by time interaction, as well as random effect on intercept and time to reflect the individual deviance at baseline and over time. The proportion of patients with stable, deteriorated, and improved HRQoL using the MID at M12, and at Y3. Each HRQoL score from the EORTC questionnaire will be analysed. The MID will be fixed to 10 points for each HRQoL score of the EORTC questionnaires. Time to improvement or deterioration of HRQoL could also be proposed in complement using Kaplan-Meier survival estimation [58, 59]. A detailed statistical analysis plan will be written for each endpoint before the data is frozen.

For the gut microbiota study, to investigate whether the gut microbiota and its metabolites mediate the positive effect of PA on CRF and other short- and long-term sequelae in metastatic TGCT patients receiving chemotherapy, we will apply two steps of statistical analyses overall: Step 1 to test “the impact of PA on the chemotherapy-induced alterations in the gut microbiota and relevant metabolites” and Step 2 to test “the effect of the gut microbiota and relevant metabolites modulated by PA on CRF and other short- and long-term sequelae in metastatic TGCT patients receiving chemotherapy”.

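### Testing each fatigue dimension at a fixed 0.025 is valid, but Holm's step-down would give more power on the second dimension at the same overall 5%

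*Protocol article*

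**What the plan says.** All references are to the protocol article.

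- **Sample size.** The calculation is made "with a bilateral alpha, type I error of 0.025 (Bonferroni adjusted" for two targeted dimensions, with an overall risk of 5%. It aims "to detect a minimum significant difference ≥ 10 points in the CRF scores between the 2 groups at 3 years" and assumes an SD of 20 and 90% power. It arrives at 200 evaluable patients and, after 15% loss, 236 randomized (118 per arm).
- **Statistical analysis.** Results are significant at 0.05 or below, "except for the primary endpoint (alpha set at 0.025"). No step-down is described. The minimal important difference is 10 points for each score.
- **Study objectives.** Objective 1 defines the "primary outcome, both physical and cognitive aspects of CRF at 3 years".
- **Decision rule.** The primary endpoint is reached if at least one of the two dimensions is significant in favour of the intervention, "in absence of a statistically significant negative result on the other dimension". The level of that negative test is not given there. The 0.025 of the Statistical analysis section applies by implication.

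**The concern.** The trial names two dimensions as its primary outcome and will report a conclusion on each. Under the fixed rule, a p-value between 0.025 and 0.05 on the second dimension has to be called non-significant, even when the first is clearly positive and the 5% overall error would permit the second claim.

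Holm's procedure tests the smaller p-value at 0.025 and, only if that is rejected, the larger at 0.05. Like Bonferroni, it needs no assumption on the correlation between the scores, and it never rejects less. What is at stake is the strength of the confirmatory statement on the second dimension. Whether the trial succeeds is not affected.

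**Working it through.** **Inputs from the protocol article:** difference 10, SD 20, two-sided 0.025 per dimension, 90% power, 15% loss, 1:1 allocation (all from Sample size). **Assumption:** the correlation ρ between the two test statistics. The document gives none, so 0.3 to 0.7 is used, with 0 as a hand check.

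**1. The plan's own figure.**
- n per arm = 2(z₀.₉₈₇₅ + z₀.₉₀)²(SD/δ)² = 2(2.2414 + 1.2816)²(20/10)² = 99.3, so 100 per arm and 200 in total.
- 200/(1 − 0.15) = 235.3, so 236, or 118 per arm.

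The stated size is reproduced.

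**2. Power of one dimension at 100 per arm.** The expected test statistic is 10/(20√(2/100)) = 3.5355.
- At 0.025: Φ(3.5355 − 2.2414) = 90.2% (89.8% with the noncentral t).
- At 0.05: Φ(3.5355 − 1.9600) = 94.2%.

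**3. Hand check at ρ = 0, 10 points on both dimensions.**
- Bonferroni, both: 0.9022² = 81.4%.
- Holm, both: each statistic must pass 1.96 and at least one must pass 2.2414. This gives 0.9424² − (0.9424 − 0.9022)² = 88.7%.
- Holm, one given dimension: 0.9022 + (0.9424 − 0.9022) × 0.9022 = 93.8%.

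**4. The same quantities under correlation** (bivariate normal probabilities, 10 points on both dimensions):

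| ρ (assumed) | Per dimension, Bonferroni → Holm | Both, Bonferroni → Holm | At least one, either method |
|---|---|---|---|
| 0.3 | 90.2% → 93.5% | 82.5% → 89.1% | 97.9% |
| 0.5 | 90.2% → 93.2% | 83.6% → 89.6% | 96.9% |
| 0.7 | 90.2% → 92.9% | 85.0% → 90.3% | 95.5% |

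The last column is the same for both methods because Holm's first step is the Bonferroni test.

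**5. Overall type I error.** With no effect on either dimension, the chance of any rejection is the same under both methods: 4.9% at ρ = 0, 4.7% at 0.5 and 3.6% at 0.9. With a 10-point effect on one dimension and none on the other, the chance of a false rejection on the null dimension is 2.5% under Bonferroni. Under Holm it is 4.3% to 4.7% for ρ = 0.7 to 0.3, still within 5%.

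**6. The negative-result guard.** Take 10 points on one dimension and none on the other, and compute the probability of success under the Decision rule:

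| ρ (assumed) | Guard at 0.025 | Guard at Holm's second-step 0.05 |
|---|---|---|
| 0.3 | 89.4% | 88.4% |
| 0.5 | 89.6% | 88.8% |
| 0.7 | 89.9% | 89.4% |

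If the guard stays at 0.025, adopting Holm leaves the probability of success exactly as it is. A benefit that Holm adds at the second step requires the other dimension to be significant at 0.025. If that other result is positive, the trial has already succeeded under Bonferroni. If it is negative, the guard blocks success under either method.

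**The case against.** The strongest reply is that nothing here is wrong. Bonferroni controls the error, the same 0.025 appears in the sample size and in the analysis, and the numbers agree. The Decision rule asks for one dimension only, so Holm adds nothing to the chance of success, and the protocol sets no power target for claiming both. Power per dimension is already the planned 90%. Fixed Bonferroni also yields plain 97.5% intervals with joint coverage of at least 95%, which is convenient for reading results against the 10-point threshold. All of this stands, and it limits the point to a recommendation.

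It does not remove the point. Objective 1 names both dimensions as primary, each has its own test and its own minimal important difference, and the extra power costs no patients and no overall error.

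Three stronger readings are tempting, and the document supports none of them:

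- *A reader might infer that the trial is underpowered because power to claim both is only 83-85%.* The design promises 90% per dimension and success on one, and it delivers that.
- *A reader might point to larger gains when the second effect is smaller.* At 8 points, power on that dimension rises from 72% to about 80%, and at 6 points from 45% to 55-56%. Both effects lie below the 10 points that the protocol calls important, so they should not carry the argument.
- *A reader might conclude that the negative-result guard should also move to 0.05, as a free gain in sensitivity.* It is not free: it lowers the chance of success when the second dimension has no true effect.

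**Conclusion.** The point holds as a cheap improvement. Under the protocol's own assumptions, and a correlation of 0.3 to 0.7 that is assumed here, Holm adds about 3 percentage points of power per dimension and about 5 to 7 points for claiming both. The overall error limit, the sample size and the chance of meeting the success rule do not change, provided that the guard stays at 0.025. Moving the guard to 0.05 would cost about 0.5 to 1 percentage point of success when the second dimension has no effect.

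The figures use a normal approximation with 100 evaluable patients per arm and ignore any gain from baseline adjustment. The exact gain depends on the correlation and on the true second effect, neither of which is known from the document.

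**What to change.** - **Sample size and Statistical analysis:** state that physical and cognitive fatigue are tested by Holm's procedure at an overall two-sided 5% (the smaller p-value at 0.025 and, if it is rejected, the other at 0.05) for claims of benefit on each dimension. The sample size calculation at 0.025 stays, since it describes the first step.
- **Decision rule:** state the level of the negative-result guard explicitly and keep it at two-sided 0.025. A negative result with a p-value between 0.025 and 0.05 would then be reported but would not block success, as under the present rule.
- **Reporting:** 97.5% intervals can still be given for each dimension. Say in advance that such an interval may include zero for a dimension that is significant only at Holm's second step.

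The cost is a few sentences, which fit the detailed analysis plan that the protocol promises before the data are frozen. No extra patients, visits or data are needed. The downside is that simultaneous intervals matching Holm's decisions are less simple than Bonferroni's.

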### Analysis population

Statistical analyses will be performed on the Intent-to-Treat (ITT) population, including all randomized patients analysed according to the randomization scheme. A sub-population will be defined for the analysis of the primary endpoint, corresponding to a modified ITT population, i.e., all ITT patients with at least the available fatigue score at baseline and 3 years.

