### Evaluation modalities

Patients will undergo several assessments during the study: at inclusion (D0), at the end of chemotherapy (end CT, about 3 months, M3), at 6 months (M6), at the end of the study intervention (one year, M12), and then annually until 10 years (Y2 ~ Y10) to evaluate potential long-term sequelae. Assessments will include clinical examination, physical assessments, self-administered questionnaires and biospecimen collection and will be performed by a physician, an adapted PA professional, and a clinical research assistant when patients come in as part of their usual disease management.

At the first assessment, the clinical research assistant will explain the study modalities to the patient. All self-administered questionnaires will be completed by patients directly via the mobile application or website. They will receive notifications via the application or by email alerting them that a new questionnaire is available and has to be completed. If the patient does not complete the questionnaires, a reminder schedule will be provided (maximum 3 reminders). If the patient does not complete the questionnaire within the time limit, it will be automatically deleted. A system of alerts on the professional interface of the STARTER website will allow the clinical research assistant to follow the completion of the questionnaires and to contact patients if needed to limit missing data. The clinical research assistant will also be able to enter the data for the patient directly on the internet platform if the patient encounters difficulties in filling out the questionnaire. A messaging system on the STARTER application will be available to patients throughout the study to communicate with the research team about study progress and assessments. PA, heart rate and sleep data from the connected activity tracker will also be collected via the STARTER application.

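### The primary analysis set is a complete-case set, so the plan's statement that an ITT analysis avoids attrition bias is unsupported for the primary endpoint

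*Protocol article*

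**What the plan says.** All references are to the protocol article.

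- **Analysis population, general rule:** "Statistical analyses will be performed on the Intent-to-Treat (ITT) population, including all randomized patients analysed according to the randomization scheme".
- **Analysis population, primary endpoint:** a sub-population is used, namely "a modified ITT population, i.e., all ITT patients with at least the available fatigue score at baseline and 3 years".
- **Statistical analysis, general paragraph:** "An ITT analysis will be used to avoid attrition bias".
- **Statistical analysis, primary test:** "A Student-t test will be used to compare the scores between the two arms at 3 years, adjusting for the level of HRQoL at inclusion". This uses the 3-year scores only, with a rank test if the distribution is not normal.
- **Statistical analysis, missing data:** "An analysis of the missing data profile at baseline and during follow-up will be performed to determine the missing data profile". The plan adds that an effort will be made to obtain the baseline and 3-year questionnaires, and gives statistical power as the reason.
- **Sample size:** 200 patients with both scores are needed. "Considering 15% of lost to follow-up or unavailable data and patients without fatigue scores available", the plan randomises 118 per group, 236 in total.
- **Table 1:** the QLQ-FA12 is scheduled at D0, M3, M6, M12, Y2 and Y3, then yearly to Y10.

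**The concern.** Under the plan's own definition, ITT keeps everyone who was randomised. The primary set keeps only those whose outcome was observed, two years after the intervention ended. Selecting on that later event is how attrition bias arises, so the analysis cannot also be the protection against it.

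Uneven loss is plausible here. The trial is open-label and the outcome is self-reported. One arm has a year of supervised sessions and four motivational interviews, and a man's fatigue may affect whether he answers a fatigue questionnaire. If the arms lose different men, the 3-year difference among completers is not the difference among those randomised. Under the Decision rule section, significance on one of the two dimensions can be enough for success, so a distortion on either one matters.

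Information is also lost. A man with every score up to Y2 but none at Y3 contributes nothing to the primary test, and neither does a man with a Y3 score but no D0 score.

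**Working it through.** **1. Reproduce the plan's sample size.** Inputs from the Sample size section: difference 10, SD 20, two-sided alpha 0.025 per dimension, power 90%, loss 15%.

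- n per arm = 2 × (z₀.₉₈₇₅ + z₀.₉₀)² × (20/10)² = 2 × (2.2414 + 1.2816)² × 4 = 99.3, rounded up to 100, so 200 evaluable.
- 100/(1 − 0.15) = 117.6, rounded up to 118 per arm, so 236 in total.
- Power with 100 per arm is 90.2% (normal) or 89.8% (noncentral t).

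The plan's figures reproduce exactly.

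**2. Size of the exclusion.** 236 − 200 = 36 patients, and 36/236 = 15.3%. This is a planning allowance, not a forecast for each arm.

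**3. Bias of a completer comparison.** In one arm let m be the missing share and G the number of points by which non-completers are more fatigued than completers. The full mean is (1 − m) × C + m × (C + G) = C + mG, so the completer mean C is too low by mG. The bias in the arm difference (intervention minus control) is −(m_I × G_I − m_C × G_C). With a common gap G this is −(m_I − m_C) × G. A negative value favours the intervention, because higher scores mean more fatigue.

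**4. Scale.** SE = 20 × √(2/100) = 2.83. Under no true effect, the chance of a significant result favouring the intervention is 1.25% per dimension. With a bias of size b in that direction it is P(Z > 2.2414 − b/SE). If the bias goes against the intervention, power is that of a noncentral t test at a difference of 10 − b.

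**5. Results.** The documents give neither missing shares by arm nor a gap, so these rows are assumptions. The larger share is placed in the intervention arm for the false-benefit column and in the control arm for the power column.

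| Missing, one arm vs other | Gap G | Bias | Bias/SE | False benefit | Power if opposite |
|---|---|---|---|---|---|
| 15% vs 15% | any, equal in both arms | 0 | 0 | 1.25% | 90% |
| 17% vs 13% | 10 | 0.4 | 0.14 | 1.8% | 87% |
| 20% vs 10% | 15 | 1.5 | 0.53 | 4.4% | 77% |
| 20% vs 10% | 20 | 2.0 | 0.71 | 6.2% | 72% |

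Using the unequal completer numbers (for example 94 and 106) leaves the SE at 2.83 and the results unchanged to this precision. Equal missing shares do not guarantee zero bias: 15% missing in both arms, with a 20-point gap in one arm only, gives 0.15 × 20 = 3.0 points.

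**6. What the 15% allowance does.** It restores the number of completers to 200 and hence the power. It does not enter the bias formula, so a larger trial with the same missing shares and gaps has the same bias.

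**The case against.** **The exception is open.** The plan states a general ITT rule and then names and defines a modified ITT set for the primary endpoint. The sample size is built on the same set. This stands: a reader might infer that the plan breaks its own ITT rule unannounced, or that a report using the modified ITT label would be untrue, and the document supports neither. What does not survive is the sentence on attrition bias. It sits in the general paragraph with no exception for the primary endpoint.

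**Missing-data methods belong in the SAP.** The Decision rule section promises a detailed SAP before data freeze. This stands too: the absence of an imputation or sensitivity method here is not the finding. The primary set, however, is already fixed in this article, and a SAP consistent with it inherits the problem.

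**Automatic deletion.** The Evaluation modalities section says "If the patient does not complete the questionnaire within the time limit, it will be automatically deleted", and a reader might infer that the app aggravates the loss. The same section provides up to three reminders, alerts to the research assistant, and staff entry of answers. It does not state the time limit, and it does not say that submitted answers are lost. No worsening can be shown.

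**The mixed model.** In the Decision rule section, "A mixed model for repeated measures will be performed including the randomized group, time, and intervention by time interaction" appears under secondary endpoints, for HRQoL. A reader might infer that fatigue is excluded. That is uncertain, because the section speaks of scores from the EORTC questionnaires and the QLQ-FA12 is one of them. It is clear only that this model is not the primary test.

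**The remedy is imperfect.** If response depends on fatigue at Y3 itself, data are missing not at random. A repeated-measures model or standard multiple imputation then reduces the bias only as far as earlier scores predict Y3. This stands and shapes the fix.

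**Conclusion.** The point holds in a limited form. The primary set is a complete-case set selected on a post-randomisation event, with about 36 of 236 patients planned to be lost. The statement that an ITT analysis avoids attrition bias is therefore unsupported for the primary endpoint, and the 15% inflation does not repair it.

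A reader might infer that the primary result will be biased, or biased towards the intervention. The document supports neither, since size and direction are both unknown. The common-gap cases shown run from zero to 2.0 points against a target difference of 10, and unequal gaps could give more. The 0.4-point and 1.5-point cases rest on assumed missing shares and gaps, an SD of 20 and about 100 completers per arm.

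**What to change.** 1. Make all randomised patients the primary analysis set.
2. For each dimension, estimate the arm difference at Y3 with a likelihood-based repeated-measures model on the M3, M6, M12, Y2 and Y3 QLQ-FA12 scores, with visit as a category, arm by visit, the D0 score and the stratification factors. Multiple imputation using the same scores is an alternative. A patient who lacks only the D0 score should stay in.
3. Keep the present completer set as a sensitivity analysis. Add a missing-not-at-random analysis, such as a delta-adjusted (tipping-point) one, because the methods in step 2 assume missing at random.
4. If the set is not changed, withdraw the attrition-bias statement for the primary endpoint.
5. Optional and secondary: accept late Y3 answers with their actual date, alongside the existing reminders, alerts and staff entry. This needs an analysis window and an app setting.

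The cost is plan wording and some programming. No extra visits are needed and N = 236 stands. Power is 90.2% with 100 per arm observed. The 94.5% for 118 per arm is an upper bound, since modelling or imputation does not recover all the lost information.
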